# Efficacy and safety of duloxetine for postoperative pain after total knee arthroplasty in centrally sensitized patients: study protocol for a randomized controlled trial

**DOI:** 10.1186/s12891-021-04168-x

**Published:** 2021-03-30

**Keywords:** Central sensitization, Duloxetine, Pain, Total knee arthroplasty

## Abstract

**Background:**

Postoperative residual knee pain after total knee arthroplasty (TKA) is a significant factor that contributes to patient dissatisfaction. Patients with preoperative central sensitization (CS) may be more susceptible to unexplained chronic pain after TKA, and duloxetine has been reported to be effective in post-TKA pain control in patients with CS. However, there remains limited evidence to support this off-label use in routine clinical practice. Hence, we designed this randomized, placebo-controlled, triple-blind clinical trial to evaluate the effects of preoperative screening and targeted duloxetine treatment of CS on postoperative residual pain compared with the care-as-usual control group.

**Methods:**

This randomized controlled trial includes patients with knee osteoarthritis on a waiting list for primary unilateral TKA. Patients with preoperative CS will be randomly allocated to the perioperative duloxetine treatment group (duloxetine group) or the care-as-usual control group (placebo group). Patients in the duloxetine group will receive a half-dose of preemptive duloxetine (30 mg/day) for a week before surgery and a full-dose of duloxetine (60 mg/day) for six weeks after surgery. The primary outcome is the intensity of residual pain at six months after TKA, including the visual analogue scale, 11-point numeric rating scale, the sensory dimension of the brief pain inventory, and the pain subscale of the Knee injury and Osteoarthritis Outcome Score. The secondary outcome measures will include the pain and function related outcomes. All of the patients will be followed up at one, three, and six months after surgery. All adverse events will be recorded and immediately reported to the primary investigator and ethics committee to decide if the patient needs to drop out from the trial.

**Discussion:**

This clinical trial will convey the latest evidence of the efficacy and safety of the application of duloxetine in postoperative pain control in CS patients who are scheduled for TKA. The study results will be disseminated at national and international conferences and published in peer-reviewed journals.

**Trial registration:**

Chinese Clinical Trial Registry (http://www.chictr.org.cn) registration number: ChiCTR2000031674. Registered 07 April 2020.

## Background

Total knee arthroplasty (TKA) is one of the most successful and effective surgical options performed in orthopedics, aiming to relieve pain and restore function for patients with end-stage knee osteoarthritis (OA) [1]. Over the past decades, significant advances have been made in TKA surgical techniques, implant design, patient selection, and perioperative care management, which led to the continuous improvement of clinical outcomes and expanded surgical indications [2–16]. Given the rapidly aging population and the growing prevalence of knee-related diseases such as OA and rheumatoid arthritis, the number of TKA procedures is projected to increase substantially worldwide [17–19]. However, the dissatisfaction rate following a TKA has persisted over the last decade, with approximately 10 %~20 % of patients remain dissatisfied following primary TKA [20–23]. As patient satisfaction has been considered a key parameter in assessing success after TKA, a substantial proportion of patients failed to achieve the desired goal of surgery [22]. Therefore, patient dissatisfaction following TKA remains a challenging problem and should be a high priority.

Previous studies have investigated the causes of dissatisfaction after TKA, and the most common reasons were residual pain and limited function [22, 24–27]. A significant number of patients remain dissatisfied as the persistent chronic pain was not relieved, even though the TKA procedure has removed the pain source [28, 29]. Recent studies found that the pain in patients with OA varies from nociceptive to neuropathic pain-(NP) like symptoms, which may contribute to joint nociceptors’ exposure to the changing biochemical environment during the process of OA [30]. It is thought that these changes might contribute to the activation and sensitization of nociceptors, lead to hyperexcitability of the central nervous system (central sensitization, CS) [29–32]. CS is defined as increased responsiveness of nociceptive neurons in the central nervous system, which is characterized by pain in the presence of a non-noxious stimulus (allodynia) and pain hypersensitivity (hyperalgesia) [33]. Not all patients with knee OA are suffered from CS, but the subgroup of patients with CS is related to low pain thresholds, high level of preoperative pain, and severe pain in the early postoperative period after TKA [34–36]. Furthermore, preoperative CS has been recently recognized as a significant risk factor for persistent pain and dissatisfaction following TKA, which could persist two years after TKA, resulting in worse quality of life, functional disability, and dissatisfaction [28, 34, 37–40]. Considering postoperative residual pain is the primary cause of dissatisfaction following TKA and CS has been identified as a risk factor for persistent postoperative pain and dissatisfaction, preoperative screening and treatment of CS could be an effective way to decrease the level of residual pain after TKA and improve patient satisfaction.

The treatment options for CS focus on those strategies that specifically target the pathophysiological mechanisms known to be involved in CS, which aim to desensitize the central nervous system. The treatment options mainly include pharmacological options (acetaminophen, serotonin-reuptake inhibitor drugs, selective and balanced serotonin and norepinephrine-reuptake inhibitor (SNRI) drugs, serotonin precursor tryptophan, opioids, N-methyl-d-aspartate (NMDA)-receptor antagonists, calcium-channel alpha(2)delta (a2δ) ligands), rehabilitation (e.g., transcutaneous electric nerve stimulation (TENS), manual therapy) and neurotechnology options (e.g., transcranial magnetic stimulation) [41, 42]. Ho et al. performed a randomized controlled trial (RCT) to evaluate the efficacy of duloxetine in reducing morphine requirements in patients after TKA and found that perioperative administration of duloxetine could reduce postoperative morphine requirements during the first 48 h after TKA, without significant differences in pain scores or adverse effects [43]. YaDeau et al. conducted a triple-blinded RCT to evaluate the efficacy of duloxetine on subacute pain after TKA, in which patients received 60 mg/day from the day of surgery for 14 days [44]. They found that duloxetine did not reduce pain at rest, with ambulation or flexion, but duloxetine could reduce opioid consumption and nausea in the first 14 days after surgery [44]. Compared with the normal controls, patients with CS are associated with more severe postoperative pain, greater opioid consumption, and a higher risk of persistent pain, so the analgesic efficacy of peri-TKA duloxetine could be more effective in patients with CS. Koh et al. conducted an RCT in patients with preoperative CS to investigate whether duloxetine could reduce postoperative pain and improve recovery quality after TKA [32]. This study suggested that in patients with preoperatively identified CS, duloxetine reduced postoperative pain and improved quality of recovery, without increasing the risk of adverse medication effects following TKA [32].

Based on previous research, for patients who are identified as having CS before TKA, supplementing perioperative duloxetine to the multimodal analgesic protocol may help to reduce postoperative pain and opioid consumption, improve the quality of recovery in terms of both emotional and physical functioning, without increasing the risk of adverse events [32, 43, 44]. However, at this time, there is insufficient clinical data to recommend routine use of duloxetine in patients with CS to ameliorate the unexplained postoperative pain after TKA. In order to tackle this knowledge gap, we designed this prospective randomized study to evaluate the efficacy and safety of preoperative screening and targeted duloxetine treatment of CS on residual pain compared with the care-as-usual control group. We hypothesized that perioperative duloxetine would reduce postoperative pain and analgesic consumption, and enhance postoperative functional recovery after TKA, without increasing the risk of adverse events in patients who are identified as having CS before TKA. We present the following article in accordance with the *Standard Protocol Items: Recommendations for Interventional Trials (SPIRIT)* reporting checklist [45].

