### Adverse events

All adverse events reported spontaneously by the patients or observed by the investigators or staff will be recorded. If any adverse event occurs, the doctor will provide the corresponding treatment to the patient. Meantime, the adverse events will be immediately reported to the primary investigator and ethics committee to decide if the patient needs to withdraw from the trial. Based on previous literature, the most common adverse events were decreased appetite, nausea and vomiting, fatigue, insomnia, constipation, and dry mouth, which could be well managed with i.v. ondansetron [32, 43, 44].

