### Sample size

Sample size calculation was performed with the VAS score as the primary outcome measure. Based on the previous study, the smallest change score for the VAS score to be considered clinically relevant is 2 points (on a 0–10 scale) between the duloxetine group and the placebo group [32]. The power calculation is performed based on the VAS score difference using a two-sided hypothesis test at an alpha level of 0.05 and a power of 80 %, and a total of 38 participants is needed in each group [57–59]. Taking into account the possibility of 20 % violators or dropouts, we will include 50 patients in each group.

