### Statistical analysis

Analyses will be performed using the IBM SPSS software (version 21.0, IBM Corp., New York, NY, USA). All outcomes measures will be assessed using both the ITT (intention-to-treat, all randomly assigned patients) and PP (per-protocol, patients who completed the trial without any protocol deviations) data sets. The missing value will be imputed by the last-observation-carried-forward (LOCF) method. For continuous variables and descriptive values, means ± standard deviations (SDs) will be reported. For the enumerative variables, frequency and corresponding percentage will be calculated. For the variables with a normal distribution, statistical comparisons between the groups will be made by using a *t*-test. For variables with a non-normal distribution or ordinal level, the statistical comparison will be made using the Mann-Whitney U test. Outcomes with a discrete distribution will be expressed as percentages and analyzed by the *chi*-squared test or Fisher’s exact test as appropriate. A *P* value < 0.05 is considered statistically significant.

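### The hypothesis that duloxetine does not increase adverse events is paired only with a test of difference at P < 0.05, with no margin and a sample size set on pain, so a non-significant result could not support it

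*Protocol article*

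**What the plan says.** Safety is in the title of the protocol article and in its stated aim: "we designed this prospective randomized study to evaluate the efficacy and safety of preoperative screening and targeted duloxetine treatment of CS". The hypothesis at the end of the Background section expects less pain and analgesic use and better function, "without increasing the risk of adverse events in patients who are identified as having CS before TKA".

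The Statistical analysis section has one rule that would cover event counts: "Outcomes with a discrete distribution will be expressed as percentages and analyzed by the" chi-squared or Fisher's exact test. The general criterion is that a P "value < 0.05 is considered statistically significant". The section does not mention adverse events by name, and it ties no margin, interval or other criterion to the safety hypothesis.

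The Sample size section is about pain only: "The power calculation is performed based on the VAS score difference". It uses a difference of 2 points on a 0–10 scale and a "two-sided hypothesis test at an alpha level of 0.05" with 80% power. This gives 38 evaluable and 50 enrolled patients per group.

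On collection, the Adverse events section states: "All adverse events reported spontaneously by the patients or observed by the investigators or staff will be recorded". It also names the expected events: decreased appetite, nausea and vomiting, fatigue, insomnia, constipation and dry mouth. It gives no rates for them.

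**The concern.** The hypothesis and the test do not match. A chi-squared or Fisher test starts from equal risk in the two arms and looks for evidence against it. A significant result would contradict the safety hypothesis. A non-significant result would leave it undecided, because the same result is expected when there is no excess and when there is an excess the trial is too small to see. No outcome of the stated analysis can therefore support the stated hypothesis.

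At stake is the safety half of the trial's conclusion. The Discussion section says that the results will supply rigorous evidence for using duloxetine in these patients. A safety statement resting on a P value above 0.05 with 50 per arm would be compatible with a substantial excess of common side effects.

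**Working it through.** **Inputs from the article.** Randomization is 1:1 between duloxetine and placebo, with 50 enrolled and 38 evaluable per group. The test is chi-squared or Fisher's exact, two-sided at 0.05. **Not given:** adverse event rates and an acceptable excess. Placebo rates of 5% to 30% are assumed below, and the 10-point margin in step 4 is only an illustration.

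**1. The plan's own sample size.** The 38 per group cannot be reproduced, because no standard deviation (SD) is stated. Solving n = 2·SD²·(1.960 + 0.842)²/2² for n = 38 gives SD = 2·√(38/2)/2.802 ≈ 3.11. The dropout allowance gives 38/0.8 = 47.5, so 48, against the stated 50. Neither figure involves adverse events, so the sample size offers no assurance about them.

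**2. Power of the stated test.** All pairs of binomial counts were enumerated, and the probabilities of the pairs with P < 0.05 were added up. The chi-squared test is without continuity correction.

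| Placebo vs duloxetine rate (assumed) | 50 per arm: Fisher / chi-squared | 38 per arm: Fisher / chi-squared |
|---|---|---|
| 10% vs 20% | 19.5% / 30.3% | 14.9% / 23.6% |
| 20% vs 30% | 15.5% / 21.2% | 11.8% / 17.3% |
| 20% vs 40% | 51.5% / 59.5% | 39.7% / 48.9% |

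With 50 per arm, a doubling from 10% to 20% is missed about 70–80% of the time. A doubling from 20% to 40% is detected slightly more often than not.

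**3. Precision when the arms look alike.** With the same observed rate p in both arms, the 95% interval for the risk difference has half-width 1.96·√(2p(1−p)/n). At p = 0.20 and n = 50 this is 1.96·√(0.32/50) = 0.157, about ±16 percentage points. At p = 0.10 it is 1.96·√(0.18/50) = 0.118, about ±12 points. An event seen in 0 of 50 patients still allows a true rate up to 1 − 0.05^(1/50) = 5.8% (one-sided 95% limit).

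**4. What a real test of no relevant increase would need.** Suppose the true rates are equal, the excess to exclude is m, one-sided alpha is 0.025 and power is 80%. Then n per arm = 2p(1−p)·(1.960 + 0.842)²/m². With m = 0.10 and p = 0.20: 0.32 × 7.849/0.01 = 251.2, so 252 per arm. With p = 0.10: 0.18 × 7.849/0.01 = 141.3, so 142 per arm. With 50 per arm, power against that margin is about 24% and 39% respectively.

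**The case against.** The hypothesis sentence can be taken as a background expectation, not as a declared non-inferiority test. Adverse events are neither a primary nor a listed secondary outcome, and most trials sized for efficacy have little power for side effects. Confidence intervals, the safety population and per-event summaries usually belong in a statistical analysis plan. These points stand as far as they go: low power for adverse events is not an error by itself, and the absence of those details is not the complaint. The mismatch remains, because the article itself fixes both the hypothesis and the only test.

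Three stronger readings are tempting and are not supported.

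- **That the sponsor will declare duloxetine safe on a non-significant result.** The article states no such rule. The Background section describes one earlier duloxetine trial as showing no significant difference in adverse effects, then cites it among trials showing no increased risk. That makes the misreading plausible here, but it is not this trial's decision rule.
- **That any doubling of a common side effect would probably be missed.** This holds for 10% to 20%. It fails for 20% to 40% with 50 per arm, where power is 52–60%.
- **That events are captured only passively.** The Adverse events section includes events observed by investigators or staff. The Follow-up period section schedules in-hospital sodium monitoring and blinded contacts at one, three and six months. The Data collection and management section assigns collection to an independent trained investigator, with oversight by a Data Monitoring Committee. Whether a symptom checklist is used is a detail that an article commonly leaves to the full protocol.

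**Conclusion.** The point holds as a mismatch between the safety hypothesis and the analysis that the article fixes. A non-significant chi-squared or Fisher result cannot support a claim of no increase, and 50 per arm leaves wide uncertainty. The interval is about ±16 percentage points if 20% of each arm have events, and power is 19–30% for 10% versus 20% and 52–60% for 20% versus 40%. The power and interval figures depend on assumed event rates; the logical mismatch does not. It should be corrected because safety is a headline aim and the correction is nearly free. The primary pain comparison and the conduct of the trial are unaffected.

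**What to change.** Reword the safety part of the hypothesis as an aim to estimate the difference in adverse event risk between duloxetine and placebo. In the Statistical analysis section, state that risk differences (duloxetine minus placebo) with 95% confidence intervals will be reported for any adverse event and for each event named in the Adverse events section. Add one sentence saying that P > 0.05 will not be interpreted as no increase in risk.

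This costs a few sentences and no extra patients or visits. The price is a weaker safety claim. Keeping a claim of no relevant increase would instead need a margin set in advance and a sample sized for it, which under the illustrative assumptions above is well beyond 50 per arm.

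Optionally, ask about the listed events in the same words in both arms at the existing contacts. This adds a short form and will probably record more minor events. The point does not depend on it.

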## Methods

### Study design

This prospective, randomized clinical trial was designed as a single-center parallel-group study with balanced randomization and enrolled patients who are scheduled for TKA. This protocol is reported following the *SPIRIT* statement [45]. This study was approved by our institutional review board and was registered at the Chinese Clinical Trial Registry (http://www.chictr.org.cn) (ChiCTR2000031674). Ethical approval for this retrospective cohort study was obtained from the institutional ethical committee (K2020005). The trial flow chart is shown in Fig. 1.

**Fig. 1 Fig1:**
[figure not shown]
CONSORT 2010 flow diagram of the study sample

### Participants

All potentially eligible participants will be selected from the consecutively recruited patients who agreed to participate. According to the inclusion and exclusion criteria, one of the authors will screen the potentially qualified participants.

### Inclusion criteria

Participants who fulfill the following criteria will be included: (I) Patients scheduled to undergo primary unilateral TKA for primary OA of the knee; (II) aged 50 years or older (CS are more prevalent in patients with a long history of knee OA); (III) had education above primary school; (VI) American Society of Anesthesiologists (ASA) physical status grade I ~ III; (V) participants who voluntarily participate in the study and sign a written informed consent form.

### Exclusion criteria

Candidates who meet any of the following criteria will be excluded from participation:

#### General exclusion criteria

(I) Received surgical knee joint procedures in the past year; (II) intra-articular knee injection or knee arthroscopy in the past three months; (III) received other surgical procedure (e.g., hip joint procedure, major thoracic or abdominal operations that may influence the assessment of CS) during the past year; (VI) planned or intended contralateral TKA procedure or any other surgical procedure within the study duration; (V) cognitive or neurological disorders that could strongly affect the questionnaire surveys (e.g., Alzheimer’s disease, dementia); (VI) inability to complete research questionnaires; (VII) with severe preoperative comorbidities that are more likely to be hospitalized during the course of the study or the illness compromises study participation significantly; (VIII) pre-existing pain (except the knee joint pain) and received relevant analgesic treatment; (IX) patients who refused to participate in the study due to stress events; (X) rejection of randomization.

#### Duloxetine‐related exclusion criteria

(I) Previous exposure to duloxetine, non-selective monoamine oxidase inhibitors, tricyclic antidepressants, selective serotonin reuptake inhibitors or SNRIs; (II) allergy to the duloxetine; (III) simultaneously usage of strong cytochrome P450 1A2 (CYP1A2) inhibitors; (IV) impaired liver function, liver cirrhosis, or liver transplantation; (V) severe renal impairment (estimated creatinine clearance less than 30 ml/min), requiring renal dialysis, or renal transplantation; (VI) history of cardiac arrhythmias, cardiac failure, myocardial infarction; (VII) personality disorder, psychiatric disorders or any major depressive disorder (based on Hospital Anxiety and Depression Scale (HADS), the cut-off point score was ≥ 11) [46]; (VIII) chronic gabapentin or pregabalin use (regular use for longer than 3 months), and chronic opioid use (regular use for longer than 3 months); (IX) a history of alcohol or other substance abuse or dependence prior to enrolment; (X) any other possible conditions that are considered inappropriate to participant in this clinical trial.

### Randomization and allocation

After applying the selection criteria, the potentially eligible patients will be screened with the Central Sensitization Inventory (CSI) preoperatively, with a CSI score ≥ 40 indicating CS and a CSI score of < 40 indicating normal [46–48]. Patients with preoperative CS will be randomly allocated (1:1) to the duloxetine group or the placebo group by a computer-generated randomization list. After randomization, there will be a baseline assessment, such as patient demographics and baseline values for outcome measures. In addition, a group of patients who are assessed as normal will receive the placebo (as the blank control group). The hospital pharmacy will prepare indistinguishable capsules containing either duloxetine or placebo for the study. Randomization and allocation will be revealed only after the required number of subjects has been recruited and the data analysis has been completed.

